## Abstract

**Background:**

Recent theoretical and empirical work has led to debate over the benefit of delaying the implementation of a decision to quit smoking in order to plan the attempt. These two need not be linked, planning can occur before a commitment to quit is made, or after it is implemented, as well as in between. This study will test whether there are independent benefits for encouraging smokers to act immediately on a definite decision to quit smoking, and to engage in structured planning.

**Methods/design:**

A complex randomised controlled trial with a factorial design, testing the presence of a recommendation to quit immediately (or not) and encouragement to structured planning (or not) as additions to standard care, a web-based automated tailored advice program (QuitCoach). Participants are recruited from users of the QuitCoach who reside in Australia, do not report a mental health condition for which they are taking medication, are adult daily smokers, and at least open to the possibility of quitting. For the Immediate arm they could not have committed to quit within 2 days, while the Planning arm included all these and those quit within the last 4 days. This creates 6 groups: 2 × 3, with 2 × 2 fully randomised, and 2 only randomised for the planning arm. Follow-up assessments are conducted around 1 month (targeting two weeks after the quit attempt started), and 6 months later. The primary outcome is 6-month sustained abstinence at 6 months. Secondary outcomes include point-prevalence abstinence at both follow-ups, and making quit attempts during the intervention period. We will also explore differences in actual behaviour (timing and planning) by intervention, and relate this to outcomes.

**Discussion:**

This study will result in a better understanding of the roles of planning and delay in influencing the success of quit attempts.

**Trial registration:**

Australian New Zealand Clinical Trials Registry http://ACTRN12612000613808

## Background

Most attempts to quit smoking fail. Borland et al. [1] recently estimated that the average smoker makes around 1 unsuccessful quit attempt per year, defining attempts as quitting for at least a day. They found around 40% reporting attempts (average around 2 each), but that at least 20% of attempts are forgotten within the year. Smokers also report a similar number of aborted attempts (plans to quit that did not achieve 1 day of abstinence). This represents a lot of failed effort. Other researchers have estimated that only 3-5% of smokers are able to achieve prolonged abstinence for 6–12 months after a given unassisted quit attempt [2], an estimate consistent with the high levels of failure. Relapse is most common within the first week [2]. Good quality structured support and advice increases smoking cessation rates over those achieved in self-managed attempts, independent of any effect attributable to use of pharmacotherapy [3], but effects of both kinds of intervention are modest. However, evidence suggests little or no success in reducing relapse beyond the early days of an attempt [4,5]. There is a need for better strategies to reduce relapse.

It is widely believed that planning for a difficult task like quitting smoking should result in increased success. The importance of planning is emphasized in stage-based models of behaviour change [6], and is implicit in models that specify the factors leading to the formation of a behavioural intention, such as the Theory of Planned Behaviour [7]. Smoking cessation guidelines for health professionals e.g., [8-10] typically recommend that smokers be encouraged to set a quit date in the future (usually 1–2 weeks later), and to prepare for this date using a range of strategies including dealing with perceived barriers to quitting, seeking social support, considering the use of pharmacotherapy or behavioural assistance, keeping a smoking diary to better understand triggers to smoke, and developing coping strategies to deal with them.

Recently, theoretical and empirical developments have led to a questioning of the primary importance of planning for quit success. PRIME theory, a comprehensive theory of addiction proposed by West [11], has drawn attention to the instability of motivation [see also [12]; Borland, forthcoming] and to the primacy of impulses and emotions in the motivational system. According to the theory, smokers may experience ‘tension’ or dissonance about their smoking over a period of time without being moved to action, until a precipitating event occurs that triggers action. When a quit effort is triggered by such an ‘epiphany’, it may be launched with a motivational momentum that increases the likelihood of success. Delaying a quit attempt following such an event in order to plan for it may be detrimental, as it can lead to a decline in motivation over the planning period, thus resulting in the attempt being made on average during a period of reduced motivation. Related to this several recent studies, using retrospective reports, have found that those who successfully quit (typically stopped for more than 6 months) have been more likely to report that their quit attempt was spontaneous, i.e. occurred as soon as the decision was made, rather than allowing a period for planning, than those who reported a failed attempt [13-17]. A study of ours found much more complex patterns with some evidence of shorter planning periods associated with less success, but no effect for longer delays [18]. Population-based retrospective studies of cutting down to quit (a form of preparatory planning and something that precludes spontaneous quitting completely) find it also results in less success than abrupt cessation, even among attempts that result in a period of cessation [19].

At this point, it is premature to conclude that delay is detrimental. The Murray et al. [15] paper provided some evidence that at least some of the effects are due to differential forgetting. Forgetting could be because a lead-in period increases the duration and thus potential salience of the event for any given length of time quit, and does this proportionately more for short attempts. Alternatively, pre-quit periods might be disproportionately likely to be forgotten with time quit as they form a smaller part of the total event. However, if the effects are real, it suggests that some forms of preparatory activity are counterproductive. Borland’s (forthcoming) dual process theory of behaviour emphasises the continually changing, environmentally cued, reactive tendency to smoke, and argues that self-regulatory functions need to be able to sustain a level of motivation for change sufficiently long for both a quit attempt to be initiated and for it to become a stable new behaviour pattern. This requires effort, which is prone to be exhausted [20,21]. As effort is required in the preparatory stages, delay will bring forward the point of exhaustion, all other things being equal. So unless preparatory activity actually leads to the task becoming easier at a faster rate than the effort involved leads to exhaustion, relapse will be more likely under conditions of delay.

Up to around half of quit attempts are reported to start immediately the decision is made [13-18]. Cooper et al. [18] also found that a minority of attempts begin after a period of abstinence for other reasons (e.g. being too ill to smoke), with only around half delaying implementation. Qualitative research [15], an in-depth empirical study following smokers on a day by day basis [12], and our own work all point to greater complexity regarding what is meant by both spontaneity and planning. First, implicit in West’s model is that spontaneity relates to peaks in fluctuating levels of longer-term concern; that is, that ‘spontaneous’ quit attempts are typically preceded by periods of deliberation that are not strong enough to trigger action, rather than occurring completely out of the blue. Certainly, a lot more smokers report thoughts of quitting than go on to try in any given period of time [1]. Second, planning may be able to be carried forward from previous, especially recent attempts. Third, our work has found that a proportion of those reporting spontaneous quits also report cutting down to quit and/or using medications (e.g., Varenicline) that require a period of use prior to stopping smoking (unpublished data). Clearly these do not represent cases of spontaneously fully implementing a quit attempt.

There is clearly ambiguity as to what constitutes a spontaneous attempt and how that relates to planning. First, what has been caught up under ideas of spontaneity really covers two quite distinct concepts: the spontaneity of the decision to quit (i.e., whether it is made without any preparatory thought or related activity); and the immediacy of implementation (i.e., whether implementation occurs immediately the decision to quit is made or with some delay). Implementation can also either refer to stopping completely (full implementation), or beginning a process that will lead to full implementation; e.g., arranging for a doctor’s appointment to get prescription medication, beginning a period of preloading with medication, or starting a cut-down schedule. Where implementation is staged, the actual quit date might not be set until reaching the target window for quitting (e.g., for Varenicline from 1–2 weeks after initiating use), and implementation could then be ‘immediate’ or sometime in the future (delayed). This analysis suggests that it may be useful to distinguish four key concepts, defining a **spontaneous attempt** as one where the decision or process of deciding is initiated without any prior forethought (at least recent); **delay in initiation** as a gap between the decision to act and the initiation of the attempt; **initiation of implementation** as beginning to perform any action necessary to the chosen approach (e.g. obtaining medication); and **full implementation** as actually stopping smoking completely.

We now turn to a similar analysis of planning, or more correctly, pre-planning, as we are not considering on-the-spot planning to deal with actual challenges. The term ‘planning’ can refer to a wide range of possible activities from simply forming some intention to act (I am planning to quit), through to various forms of preparatory activity. The research referred to above has tended to assume that planning must occur before action, and that spontaneous attempts preclude the possibility of planning. It is true, where a spontaneous decision is fully implemented immediately, that there is no opportunity to pre-plan a quit attempt. Otherwise, there is the possibility of conditional planning (i.e. before deciding to quit) or of engaging in planning between making the decision and full implementation. However, while delay provides the opportunity to plan, it does not mean it will happen.

There are some aspects of planning that must by necessity occur before full implementation, such as deciding on how to quit (abruptly or by cutting down), whether to use help such as Varenicline that should start before actually quitting, and planning activities like keeping diaries of cigarettes smoked. However, many aspects of planning can equally occur before or after quitting, such as planning for high-risk situations and seeking social supports. Anticipating and forming strategies to deal with events that may precipitate relapse can occur after a quit attempt has started, though situations that will be encountered early on, such as dealing with strong situational cravings, would have to be prioritized. Assuming the person is not already craving a cigarette when they make the decision to quit, they should have some time to plan before any serious cravings occur, and except for the minority who experience almost continual cravings, should have time between bouts of craving to plan for future instances, even if they have to deal spontaneously with a couple of unplanned-for episodes of craving before their planning is complete. Certainly, the notion that the sequence must be to decide, plan, then implement is by no means a necessity, and what limited data we have suggests it is by no means the norm. There is also no good evidence as to whether the timing of these activities has any effect on their utility.

It is also plausible that the quality of planning is at least as important as its presence. Recent research has shown that a form of planning called an implementation intention can improve outcomes [22]. An implementation intention is a self-statement of the form when or if some specified event occurs, I will engage in some specified protective action; e.g., ‘when I get a craving to smoke while with my friend Jim, I will remind him that he has agreed to help me stay quit’. A meta-analysis of 94 studies found forming implementation intentions to have a medium-to-large effect on goal attainment, over and above the impact of forming relevant goal intentions [23]. More recently implementation intentions have been shown to facilitate ongoing goal striving (relapse prevention), protecting individuals from the influence of potentially disruptive inner states such as cravings [24]. It appears to be a new and important strategy for getting people to implement plans at the appropriate time. That said, all of the studies to date have either been of relatively straight-forward behaviours, or have only considered short term outcomes for more complex ones like smoking.

This study is designed to test (a) the potential benefit of structured support for planning, and (b) the potential benefit of recommending an immediate start to the implementation of a quit attempt.

Conducting RCTs of events where choice is under the control of smokers rather than researchers/clinicians is always complicated and often requires compromise. It is particularly problematic when smokers’ spontaneous choices might contribute to the therapeutic effect. We cannot randomize spontaneity, but independent of whatever pre-decisional planning smokers have engaged in, we can randomize to encouragement to quit at one time or another, and to the provision of structured help to facilitate planning, but are limited in our ability to constrain the timing of the planning that is undertaken.

Advising people to stop smoking immediately is unlikely to be a sensible intervention strategy because it precludes use of the forms of help that require a period of pre-quit use (e.g. Varenicline). Immediate implementation is defined here as immediately taking whichever ‘next step’ is required to ensure that the quit attempt takes place without avoidable delay, and only for some will this be stopping immediately. We will record instances of unavoidable delay, to see if this makes a difference.

In this study, we will recruit a group of smokers at a time when their motivation to quit is high, and at the point at which they seek cessation assistance, but who are not sufficiently advanced in their progress towards becoming an ex-smoker to preclude the provision of either or both interventions. The use of web-based cessation help is an ideal setting, as smokers can access it when considering quitting and there need be no delay. While some smokers access this form of help after quitting, most do so before, including many who have not yet committed to an attempt [25]. The QuitCoach [26], a demonstrably effective Internet-based automated tailored advice program developed by the authors [27], is designed to assess a smoker’s situation and provide immediate assistance. Users complete a 10-minute online assessment and receive tailored advice based on their answers, which can either be read on screen or downloaded as a PDF document. The program is designed to be used on multiple occasions, with return to the site recommended after a significant change has taken place, such as actually initiating a quit attempt, or to prevent relapse.

The primary hypotheses are that among smokers who seek help from QuitCoach, 6 month sustained abstinence will be greater among:

1. those encouraged to begin to implement a quit attempt immediately as compared with those supported to quit to their own timetable); and

2. those who are provided with a structured planning program with prompts to engage in planning activities and encouragement and supported to form implementation intentions as compared with those only provided motivational messages and general encouragement to plan.

Secondary aims are to:

1. test for any interaction between the two interventions, particularly to see if the two add value when combined;

2. test the hypothesis of a dose–response relationship for actual use of the planning resources and with other planning activity;

3. test whether more dependent smokers will be more likely to benefit from the planning intervention;

4. test whether smokers with a recent history of quit attempts and those who report at baseline that they have already engaged in planning will be less likely to benefit from the planning intervention; and

5. explore the relative benefits of the timing of planning (e.g., more before vs more after) on success.

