**Integration of the two interventions (IP group)** Because the Structured Planning intervention is tailored to any level of immediacy in quitting, there is nothing unique about this group except that more will be doing their planning after the initiation of their quit attempt and more after full implementation (as will the XP group).

**Common elements** Frequency of use of the QuitCoach is at the participant’s discretion, regardless of which of the four possible study arms they have been randomised to. Thus, there is no set endpoint for delivery of the intervention. All participants will be reminded to return to the site via emails sent periodically over several weeks, scheduled according to their readiness to quit.

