#### Assessment tools

We collect research information at three points: 1) at baseline, incorporated into the QuitCoach assessment (nearly all questions used are part of the standard assessment); 2) a first follow-up two weeks after the estimated quit date for each participant, or where the quit date is unknown or a quit date has not been set, a month after recruitment; and 3) A final follow-up 6 months after the identified quit date for each participant, or a comparable time after recruitment if no quit attempt was reported at the initial follow-up. Follow-up assessments will be conducted over the Internet, using email invitations including a web link to prime respondents to do the surveys online, or for those failing to respond to this, by telephone interview (the emailed invitation includes a notification that those failing to respond will be called).

The QuitCoach assessment, used as the baseline survey, includes validated measures of sociodemographics, quitting history, intention to quit [29], self-efficacy to quit [29], nicotine dependence [30], pros and cons of smoking and temptations to smoke [31], determination to quit [32] and a 5-item measure of positive and negative affect. All of these are used in the advice tailoring algorithms. To this we have added measures of rated quality of life, health status, perceived usefulness of planning, and the extent to which planning has already taken place on the current quit attempt (prior to recruitment). The base assessment will also ask for residential details (i.e., postcode) with which to determine socio-economic status as measured by SEIFA levels of area disadvantage [33].

At the first follow-up, we will assess smoking status, including implementation of the suggested quit date and actual quit date. We will ask about the extent of any planning undertaken since the baseline survey both pre- and post-full implementation of quit attempts (as relevant). We will measure use of other cessation support and use of pharmacotherapy (both pre-and post-implementation). The questions on affect will be re-asked in order to assess stability of mood. Finally, among those quit, we will measure self-efficacy to stay quit, extent of cravings [34], and determination to stay quit [32].

The final (6-month) follow-up will be restricted to measuring outcomes; smoking status, duration of time quit, and any lapses.

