Engagement with the intervention will also be measured using naturally collected unobtrusive objective measures of program use [35], using web server log files and session identifiers linked to individual login names. Data collected will include the number of QuitCoach assessments completed and partially completed, number of log-ins to the site, number of openings of the advice page, To Do List and Problem Planner, number of edits of the To Do List, and number of times the additional resources page is viewed.

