#### Sample size calculation

As noted earlier, we expect that a minority of participants will not comply with the recommendations to which they had been randomised. Based on levels of intervention usage achieved in a previous study in which participants were offered use of QuitCoach, a text messaging program or a combination [36], we anticipate at least 50% of those offered a program of structured planning will undertake a criterion level of planning (defined as one or more of seeking social support, practicing replacement strategies, or forming plans for coping with challenges, as reported at the first follow-up), whereas less than 5% of those in the IC and CC conditions will do so. We expect around 60% acceptance of the immediate implementation recommendation. This effectively means that the real effect of the intervention will be around twice the observed difference, which must be taken into account in power calculations.

We consider a 5% difference in absolute success rates (6 month sustained abstinence) to be highly significant. The expected base cessation rate for the control group (CC) is 18%, based on a comparable group from [28]. We propose a sample size of 600 per group (1200 per main effect comparison), which will provide 86% power to find a 5% increase in the success rate (23%) in the IC and CP conditions. We will have 98% power to find a 10% increase in the success rate (28%) in the IP condition over the CC condition, assuming no interaction. We have 80% power to find a difference of 6.6% between the IP and CC conditions [37]. A total sample size of 2400 across the 6 groups (i.e., with 800 per main effect comparison, with 800 in the XP and XC conditions combined) provides 68% power to find a 5% increase in the success rate in the IC and CP conditions.

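### Secondary aims 2 and 5 relate planning to sustained abstinence using a planning measure that includes post-quit planning, so part of the exposure is a consequence of the outcome

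*Protocol article*

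**What the plan says.** The secondary aims, at the end of the Background, include two analyses of observed planning. Aim 2 is to "test the hypothesis of a dose–response relationship for actual use of the planning resources and with other planning activity". Aim 5 is to "explore the relative benefits of the timing of planning (e.g., more before vs more after) on success". The sample size section equates success with 6-month sustained abstinence.

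The exposure comes from two sources described under Assessment tools:

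- **Self-report.** Planning is asked about at "a first follow-up two weeks after the estimated quit date for each participant", or a month after recruitment where no quit date is known. The question covers "the extent of any planning undertaken since the baseline survey both pre- and post-full implementation of quit attempts (as relevant"). The criterion level of planning in the sample size section is likewise taken "as reported at the first follow-up".
- **Server logs.** These include the "number of openings of the advice page, To Do List and Problem Planner, number of edits of the To Do List". No closing date for the counts is given. Under Interventions, Common elements, the article adds: "Thus, there is no set endpoint for delivery of the intervention".

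The Outcomes and data analysis section describes the link between these actions and success as prospective. It keeps the primary analysis by allocated condition, whatever the compliance. The Background notes that relapse is commonest in the first week.

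**The concern.** The abstinence clock starts at the quit date, while post-quit planning is counted from that date until the first follow-up, or longer in the logs. The exposure and outcome windows overlap in the period when most relapse occurs.

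Two things follow. A participant who never stops smoking has no post-quit planning and no sustained abstinence, both by construction. A participant who relapses on day 2 has two days in which to plan while quit, against fourteen for a sustained abstainer by the survey and about six months in uncapped logs. Unless relapsers keep planning at the same rate, success raises the measured exposure. This is immortal-time bias, and the word prospective does not fit the post-quit part of the measure.

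What is at stake is the reading of aims 2 and 5. The Discussion says the study will inform advice on how best to configure quit attempts, and a spurious gradient in amount or timing of planning could feed into that.

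**Working it through.** The article gives no figure for these analyses. Its figure for the primary comparison (18% v 23%, 1200 per side, 86% power) reproduces at 85.9% with two-sided alpha 0.05 assumed, and is not in question. The check is what the odds ratio (OR) would be if planning had no effect.

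**Inputs.** From the article: 18% overall success and a first follow-up at about day 14. Assumed, not in the article: 80% start an attempt; 18% of all participants sustain it, so 80 − 18 = 62% start and relapse and 20% never start; relapse times are exponential with median 7 days, λ = ln 2/7 = 0.0990 per day; planning acts occur at 0.5 per week while abstinent, μ = 1/14 = 0.0714 per day; after relapse the rate is kμ.

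**Exposure: any post-quit planning by day 14.**

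Sustained abstainers: 1 − exp(−14μ) = 1 − exp(−1) = 0.632.

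Relapsers: with a = λ + (1 − k)μ, P(none) = exp(−k) × [(λ/a)(1 − exp(−14a)) + exp(−14a)].

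For k = 0 (planning stops at relapse): a = 0.1704, exp(−14a) = 0.092, λ/a = 0.581, so P(none) = 0.581 × 0.908 + 0.092 = 0.620 and P(any) = 0.380.

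- Among starters: OR = (0.632/0.368) ÷ (0.380/0.620) = 2.8.
- Among everyone, adding the 20% who never start to the unexposed failures: OR = [0.18 × 0.632 × (0.62 × 0.620 + 0.20)] ÷ [0.18 × 0.368 × 0.62 × 0.380] = 4.3.

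The same formulae for other values of k:

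| Planning rate after relapse | P(any), relapsers | OR, starters | OR, everyone |
|---|---|---|---|
| none (k = 0) | 0.380 | 2.8 | 4.3 |
| half (k = 0.5) | 0.530 | 1.5 | 2.6 |
| equal (k = 1) | 0.632 | 1.0 | 1.9 |
| 1.5 times (k = 1.5) | 0.703 | 0.73 | 1.5 |

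**Uncapped logs.** Over about 26 weeks a sustained abstainer has a mean of 13 acts, so P(any) = 1 − exp(−13), which is essentially 1. A relapser with k = 0 has μ/(λ + μ) = 0.42. Virtually every success would then count as a planner.

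**A wider measure, closer to the aims.** A null simulation (600,000 people per scenario, 18% success) added pre-quit planning (mean 0.5 acts) to post-quit planning (mean 1 act per 14 abstinent days), with 40% to 60% of attempters abstinent at day 14.

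| Scenario | OR, any planning | OR, more after v more before |
|---|---|---|
| All attempt, planning stops at relapse | 1.5 to 1.95 | 1.4 to 1.9 |
| All attempt, relapsers at half rate | 1.2 to 1.4 | 1.2 to 1.3 |
| All attempt, equal rate | about 1.0 | about 1.0 |
| All attempt, relapsers at 1.5 times | 0.8 to 0.9 | 0.8 to 0.9 |
| 15% to 30% never attempt, planning stops at relapse | 2.0 to 3.0 | 1.85 to 3.3 |
| 15% to 30% never attempt, equal rate | 1.4 to 2.0 | 1.3 to 1.7 |

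**Repairs under the same null.** Pre-quit planning among attempters gave 0.98 to 1.01. Post-quit planning by day 14 among those abstinent at day 14 also gave 0.98 to 1.01: everyone in that set has had the same 14 days in which to plan.

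**A fixed window from randomisation.** For someone who quits on the day of randomisation, a 14-day window is the day-14 count in the first table, with OR 1.5 to 2.8 among starters when relapsers plan at half rate or not at all. Fixing the window does not by itself remove the bias.

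**The case against.** Aims 2 and 5 are single lines. They set no model or analysis set, and no sentence says that whole-trial log counts will be regressed on sustained abstinence; the statement about no endpoint concerns delivery. Landmarks and cut-offs are ordinary content for an analysis plan, which is not shown. Self-reported planning already stops at the first follow-up, and the final survey records outcomes only. Much planning does not depend on being quit: the Background says many aspects can take place on either side of the quit date, and only one To Do List item is reserved for those who have quit.

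Much of this stands. The six-month figure applies only if the logs are left uncapped. The measure mixes affected and unaffected planning, so the OR of 4.3, which isolates post-quit planning, is an upper illustration. What does not stand is that this is only missing detail. The article itself places post-quit planning in the exposure, measures it after the outcome clock has started, and calls the relation prospective. Stopping at the first follow-up limits the bias but does not remove it, because early relapse falls inside that window.

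A reader might infer that these analyses will favour planning whatever the truth, or that the trial's central claims are compromised. Neither is supported. The bias vanishes or reverses under some relapser behaviour, and the two primary hypotheses are tested by randomised condition.

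**Conclusion.** The point holds for secondary aim 2 and exploratory aim 5, and only for the post-quit component of planning. The expected direction is towards more planning, and more planning after quitting, with no true effect. Null odds ratios of about 1.2 to 4 arise when relapsers plan less than abstainers or when non-attempters stay in the comparison. The value is near 1 only if the analysis is confined to attempters and relapsers plan as much as abstainers; it can fall below 1 if relapsers plan more. These sizes rest on assumed attempt, relapse and planning rates, so the direction is better supported than any one value. Planning before the quit date, the randomised primary comparisons and the sample size are unaffected. It should be corrected before analysis, but does not threaten the main result.

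**What to change.** 1. **Aim 2.** Either relate planning recorded before the quit date to outcome among those who make an attempt, or count planning and log use only up to the first follow-up and model later abstinence among those abstinent at that point. Do not rely on a fixed window from randomisation alone.
2. **Aim 5.** Use the same landmark at the first follow-up for the before-versus-after comparison. The survey is not at the same interval after quitting for everyone, so take account of days since quitting at the landmark.
3. **Both.** Stop log counts at the landmark and report the results as associations. Base any causal statement about planning on the randomised planning assignment.

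The first survey and session logs already supply the data, so the cost is analysis wording. The landmark set is smaller, addresses only relapse after about two weeks although relapse is commonest in the first, and conditions on early abstinence, so possible selection should be acknowledged. The pre-quit analysis answers a narrower question, since it says nothing about planning after quitting.
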